## Abstract

**Background:**

Pregnancy is a period in the life of women that is often associated with decreased daily physical activity and/or exercise. However, maintaining adequate levels of daily physical activity during pregnancy is important for mother and child. Studies suggest that moderate daily physical activity and exercise during pregnancy are associated with reductions in the risk of gestational diabetes mellitus (GDM). However, at present, physical activity is not routinely advised to pregnant women at risk for gestational diabetes in the Netherlands. In FitFor2-study we aim to assess whether an exercise program can improve insulin sensitivity and fasting plasma glucose levels of women at high risk for gestational diabetes, assuming that this will lower their risk of gestational diabetes.

**Methods:**

The FitFor2-study is a randomised controlled trial. Women who visit one of the participating hospitals or midwifery practices and who are at risk for gestational diabetes are eligible to participate. After baseline measurement they are randomly allocated to in the intervention or control group. The intervention group receives an exercise program twice a week in addition to usual care. The exercise program consist of aerobic and strength exercises and takes place under close supervision of a physiotherapist. Data are collected at 15, 24 and 32 weeks of pregnancy and 12 weeks after delivery. Primary maternal outcome measures are fasting plasma glucose and relative increase in insulin resistance. Primary neonatal outcome is birth weight. Secondary outcome measures are: maternal serum triglycerides, HDL, cholesterol, HbA1c, maternal weight gain during pregnancy, maternal physical activity level, foetal growth.

**Discussion:**

If the FitFor2 intervention program proves to be effective, obstetricians and midwives should refer women at risk for GDM to a special exercise program. Exercise programs for pregnant women under supervision of an experienced trainer are already available in the Netherlands, and these programs could be adjusted easily for this target group. Furthermore, the costs of these programs should be refunded by including them in the basic health care cost reimbursement schemes.

**Trial registration:**

NTR1139

## Background

In 2007, the Centers for Disease Control and Prevention (CDC) and the American College of Sports Medicine (ACSM) have recommended that all healthy adults aged 18 to 65 yr accumulate moderate-intensity aerobic (endurance) physical activity for a minimum of 30 minutes on five days each week or vigorous-intensity aerobic physical activity for a minimum of 20 minutes on three days each week. Combinations of moderate- and vigorous-intensity activity can be performed to meet this recommendation [1]. Physical inactivity is a major risk factor for cardiovascular and obesity-related diseases, such as hypertension, atherosclerosis, and diabetes mellitus type 2 [2].

Pregnancy is a period in the life of women that is often associated with decreased daily physical activity and decreased participation in sports and exercise [3]. Ning et al. reported that 23% of previously active women ceased to engage in exercise completely during pregnancy [4]. Factors that might influence the level of physical activity during pregnancy are, for instance, early pregnancy symptoms, such as nausea and fatigue or the perception that physical activity during pregnancy is risky to maternal or foetal health [3]. In the absence of either medical or obstetric complications, the American College of Obstetricians and Gynaecologists (ACOG) recommended 30 minutes or more of moderate exercise on most, if not all, days of the week for pregnant women.

A reduction in daily physical activity levels and lack of exercise is not the only change during pregnancy. Many physiological changes occur: in body weight, the vascular system, and in hormonal and energy balance. Shifts in maternal metabolism result in an increased insulin resistance during pregnancy. In women with a suboptimal beta-cell function, the increase in insulin secretion may not be sufficient to compensate the increased insulin resistance, resulting in gestational diabetes mellitus (GDM) [5]. GDM is defined as carbohydrate intolerance of varying degrees of severity with onset or first recognition during pregnancy and disappearance after pregnancy. GDM is associated with an increased maternal risk for other pregnancy-related complications, such as pre-eclampsia, postpartum haemorrhage, and with an increased risk for developing type 2 diabetes after pregnancy [6]. It also puts the infant at risk, since gestational diabetes is associated with an increased risk for macrosomia, jaundice and birth trauma [6]. Later in life, children of gestational diabetic mothers have an increased risk for obesity, abnormal glucose tolerance, and type 2 diabetes [6].

In Western countries, the most common treatment for women with GDM is dietary advice and secondly insulin treatment. Although regular daily physical activity and/or exercise is an established therapeutic adjunct in type 2 diabetes mellitus in non-pregnant adults, it is not routinely offered to women with GDM. This is because physicians and the mothers worry about several maternal physical responses during exercises that may be negatively affect the foetus [8]. Potential adverse effects could be growth retardation, premature labour, foetal trauma [7]. However, no such ill-effects of moderate physical activity or exercise have been found in the literature [7-10].

The importance of regular physical activity for glycaemic control in women with GDM has already been shown repeatedly. The increased insulin resistance normally occurring during pregnancy can be reduced by increased levels of moderate intensity daily physical activity [11,12]. Already in 1989, Jovanovic-Peterson et al. [13] showed in a clinical trial that glycaemic control in women with GDM was improved after treatment with an exercise program, similar to improvements obtained with pharmacological therapies. These results were confirmed later by others [14-16]. However, most of these trials studied the effects of a short term exercise program (i.e. a single bout or only several weeks). Studies on longer lasting exercise programs, especially those continuing into the third trimester of pregnancy, are currently lacking. Furthermore, most studies concerned the treatment, and not the prevention of GDM.

Only case-control and cohort studies are available as evidence for a positive effect of regular physical activity and/or exercise in the prevention of GDM [17-19]. However, there are no reasons to suggest that the underlying mechanisms for GDM are any different than for type 2 diabetes mellitus in non-pregnant individuals. Since daily physical activity and/or exercise has been shown to be effective in the prevention of type 2 diabetes in high-risk adults [20], it is plausible that it will also be an effective strategy for the prevention of GDM.

So, based on the literature, increasing levels of daily physical activity and/or participation in an exercise program during pregnancy may be an effective strategy for the prevention of GDM. However, at the moment, such a regime is not routinely advised or prescribed for women at risk for GDM in the Netherlands.

Consequently, in the FitFor2-study the effects of an exercise program for women with an increased risk for GDM on fasting blood glucose levels, insulin resistance, and foetal birth weight in women with an increased risk for GDM will be determined. The overall aim of the FitFor2 study is to assess whether an exercise program can improve insulin sensitivity and fasting plasma glucose levels of women at high risk for gestational diabetes, assuming that this will lower their risk of GDM. Secondary objectives are a cost-effectiveness analysis and a process evaluation (i.e. assessing the compliance with the exercise program and what factors contribute to the success or failure of the program). The aim of this paper is to describe the design of a randomised controlled trial, the FitFor2 study.

## Methods

### Study design

This study is designed as a randomised controlled trial (RCT), to assess whether an exercise program improves insulin sensitivity and fasting plasma glucose levels of women at high risk for gestational diabetes, assuming that this will lower their risk of GDM. The design is presented in Figure 1. The Medical Ethics Committee of VU University Medical Centre at Amsterdam has approved the study design, protocols, and informed consent procedure. All participants must provide a written informed consent. After baseline measurements, participants will be randomly allocated to the control or intervention group. The participants will be followed for 9 months: from 15 weeks of pregnancy until 12 weeks after delivery.

**Figure 1 F1:**
[figure not shown]
**Study design**.

### Study population

Participants will be pregnant women at increased risk for gestational diabetes. Women will be considered to be at increased risk for GDM if they are obese (BMI ≥ 30) or overweight (BMI ≥ 25) AND have at least one of the three following characteristics [21,22]:

1) history of macrosomia (offspring with a birth weight above the 97^th ^percentile of gestational age);

2) history of abnormal glucose tolerance during previous pregnancy;

3) first grade relative with diabetes mellitus type 2.

### Setting

This trial will be carried out in 10 midwifery practices and 3 larges hospitals in Amsterdam, The Netherlands. The midwives and obstetricians working in these practices or hospitals will invite women to participate in the study from October 2007 until December 2009.

### Inclusion and exclusion criteria

Pregnant women at increased risk for gestational diabetes will be eligible to enter the study when they meet the following inclusion criteria: between 14 and 20 weeks of pregnancy; over 18 years of age; sufficiently fluent in Dutch; being able to be moderately physically active; and willingness to give written informed consent.

Women will not be admitted to the RCT if they meet any of the following exclusion criteria: diagnosed with (gestational) diabetes mellitus before randomisation; hypertension (systolic pressure > 160 mmHg and/or diastolic pressure > 100 mmHg); alcohol abuse (i.e. 2 glasses alcohol or more per day); drug abuse (except for incidental analgesic agents); use of the medication that affects insulin secretion or insulin sensitivity (antiviral, corticosteroids, antihypertensive drugs, all concomitant medication will be discussed); serious pulmonary (COPD, exercise-induced asthma), cardiac, hepatic or renal (serum creatinine < 150 μmol/l) impairment; malignant disease; serious mental or physical impairment i.e. preventing to understand or implement the study protocol/aim.

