### Recruitment

Women will be recruited at the Departments of Obstetrics of VU University Medical Centre (VUMC), St. Lucas Andreas Hospital (SLAZ) and Onze Lieve Vrouwe Gasthuis (OLVG) in Amsterdam and 10 midwifery practices in Amsterdam. The obstetricians or midwives in the 3 hospitals and midwifery practices will introduce the study at the first visit of every pregnant woman who is eligible for inclusion. They will give the pregnant women who are interested to participate a brochure about the study to read at home. Obstetricians and midwives will also fill out a reply coupon (name, telephone number, inclusion and exclusion criteria) and will send this coupon to the research team. Interested women can return the informed consent form to the research team or the research team calls within two weeks after receiving the reply coupon. When women meet the inclusion criteria and want to participate, they will be included. After inclusion, an appointment for the baseline measurement will be made.

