### Sample size

Power analysis is based on the effects of the intervention program on fasting plasma glucose. A difference of 0.4 mmol/l in fasting plasma glucose between the two research groups is considered to be clinically relevant. Assuming a standard deviation of 0.7 mmol/l, this difference can be detected with a power (1-β) of 0.80 and an alpha of 0.05 with two groups of 64 subjects. Taking a loss to follow up of about 20% into account, a total of 160 subjects will be recruited. A significant difference of 300 grams in birth weight can also be detected with this number of participants, assuming a standard deviation of 600 grams.

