#### Laboratory tests

##### • Fasting blood samples

Fasting blood will be drawn from the antecubital vein after a participant has fasted for at least 10 hours. From this blood samples glucose, HbA1c, HDL-cholesterol, triglycerides and cholesterol will be measured. HDL-cholesterol, triglycerides and cholesterol will be measured by means of enzymatic techniques (Boehringer-Mannheim, Mannheim, Germany). HbA1c will be measured by High Performance Liquid Chromatography. Plasma glucose will be measured in plasma by means of a hexokinase-method (Roche Diagnostics GmbH, Mannheim, Germany).

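### The renal exclusion defines serious impairment by a creatinine value whose inequality sign contradicts the word it defines

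*Protocol article*

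**What the plan says.** The section on inclusion and exclusion criteria in the protocol article introduces its exclusions with "Women will not be admitted to the RCT if they meet any of the following exclusion criteria", so meeting any single item is enough to bar a woman from the trial.

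One item covers serious organ impairment and includes "cardiac, hepatic or renal (serum creatinine < 150 μmol/l) impairment". The parenthesis is the only definition of renal impairment in the article. The same sentence contains another exclusion based on a clinical measurement: "hypertension (systolic pressure > 160 mmHg and/or diastolic pressure > 100 mmHg".

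The Study population section describes the target group: "Participants will be pregnant women at increased risk for gestational diabetes". Risk is defined there by body mass index and history. No renal condition is part of it.

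Under Recruitment, obstetricians and midwives "fill out a reply coupon (name, telephone number, inclusion and exclusion criteria", and send the coupon to the research team.

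**The concern.** The number in the parenthesis is there to say when renal impairment counts as serious. A value on the low side of a creatinine limit cannot do that, because impairment shows as a raised value. The rule in words and the rule in figures therefore point in opposite directions.

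This is an entry criterion, not background text. It governs admission to a trial of supervised aerobic and strength exercise, so it helps to define the population and plausibly serves safety as well. Someone who works from the figure alone would turn away women without impairment and pass women with it. As printed, the criterion also cannot be used to audit eligibility, to repeat the trial or to say to whom its results apply, unless the reader first decides which half to believe.

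**Working it through.** No formula applies, and the plan gives no derived figure to reproduce. The check is a literal reading of the criterion, set against the text around it. It uses one piece of general knowledge that the article does not state: serum creatinine rises as renal function falls.

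**Step 1. Literal reading.** The list excludes anyone who meets an item. The two sides of the limit come out as follows.

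| Serum creatinine | Meets the criterion as printed? | Result on this criterion | Side of the limit |
|---|---|---|---|
| Below 150 μmol/l | Yes | Not admitted | Unimpaired side |
| 150 μmol/l or above | No | Admitted | Impaired side |

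The last column is the reverse of what excluding serious impairment requires.

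**Step 2. Could the figure be a permitted value?** It could be if it stood in the inclusion list. It stands among the exclusions and qualifies the word impairment, so that reading is not open.

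**Step 3. The list's own convention.** The hypertension item, "hypertension (systolic pressure > 160 mmHg and/or diastolic pressure > 100 mmHg", puts the sign on the abnormal side. The alcohol item also excludes from its limit upwards. The renal item is the only one with a numerical limit whose sign points to the normal side.

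**Step 4. Fit with the target population.** The inclusion criteria require no renal impairment, and the woman must be able to be moderately active. Taken literally, the renal item would bar the unimpaired women whom these criteria describe.

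**Step 5. Correction elsewhere.** No other section mentions creatinine or renal function. The laboratory section says: "From this blood samples glucose, HbA1c, HDL-cholesterol, triglycerides and cholesterol will be measured". Creatinine is not on that list, and the article does not say how the renal criterion is checked.

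**Step 6. Reach into the statistics.** The power statement, "this difference can be detected with a power (1-β) of 0.80 and an alpha of 0.05 with two groups of 64 subjects", rests on a difference of 0.4 mmol/l in fasting glucose and a standard deviation of 0.7 mmol/l. Neither depends on the renal criterion, and the regression plan does not use it.

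**The case against.** The strongest reply is that any clinician would see what is meant. The words serious impairment stand in the same phrase, and screening is done by obstetricians and midwives, who are unlikely to take a low creatinine for renal disease. The text is also a journal article that condenses a full protocol not shown here. The ethics committee approved the study's protocols, and the slip may exist only in print. A fault in reading the PDF cannot be ruled out either, although the other inequality signs in the same sentence came through intact. All of this stands as a limit on the harm. It does not remove the contradiction in the published text.

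The documents do not support four stronger conclusions that a reader might draw:

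- **That the error reached all 10 midwifery practices and 3 hospitals through the coupon.** The Recruitment section shows that the coupon covers the criteria. It does not show that the creatinine figure or this sign is printed on it.
- **That every enrolled woman is a formal eligibility deviation.** A woman without serious renal impairment does not meet the criterion in words. Because words and figure conflict, the text does not make her a clear deviation. Creatinine is also not among the listed trial blood tests, so a value may not exist for each woman.
- **That an eligibility-based analysis set is at risk.** The Statistical analysis section specifies intention-to-treat and defines no such set.
- **That recruitment would fail.** This would follow only if sites applied the figure literally and ignored the words. Nothing in the article suggests that they do.

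**Conclusion.** The point holds as an internal contradiction in an eligibility rule. The sign in the renal exclusion marks the side opposite to the impairment that it defines, and the article contains no correction. It concerns one character in one criterion. On a literal reading the effect of that criterion is fully reversed. Given the recoverable intent, the effect in practice may be nil, and the article gives no means of telling. The sample size of 64 per group, with 160 to be recruited, and the planned analysis do not change.

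The conclusion rests on two assumptions: that the sign was printed as it appears here, and that creatinine rises with renal impairment. It takes no view on what renal limit should apply.

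**What to change.** Compare the sentence with the approved full protocol and reconcile the sign with the word impairment. The clinical lead should confirm both the sign and the threshold, since this review proposes neither. If the full protocol is already consistent, a correction to the article is enough.

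Then check whether the reply coupon and any site eligibility form carry the same sign. If they do, correct them, send the sites a short note and review the forms already completed. If they do not, record that and stop there.

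The cost is a one-character correction and a brief document check. A note to the sites and a review of completed forms are needed only if the error is found there. No sample size or analysis work follows.

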### Recruitment

Women will be recruited at the Departments of Obstetrics of VU University Medical Centre (VUMC), St. Lucas Andreas Hospital (SLAZ) and Onze Lieve Vrouwe Gasthuis (OLVG) in Amsterdam and 10 midwifery practices in Amsterdam. The obstetricians or midwives in the 3 hospitals and midwifery practices will introduce the study at the first visit of every pregnant woman who is eligible for inclusion. They will give the pregnant women who are interested to participate a brochure about the study to read at home. Obstetricians and midwives will also fill out a reply coupon (name, telephone number, inclusion and exclusion criteria) and will send this coupon to the research team. Interested women can return the informed consent form to the research team or the research team calls within two weeks after receiving the reply coupon. When women meet the inclusion criteria and want to participate, they will be included. After inclusion, an appointment for the baseline measurement will be made.

### Sample size

Power analysis is based on the effects of the intervention program on fasting plasma glucose. A difference of 0.4 mmol/l in fasting plasma glucose between the two research groups is considered to be clinically relevant. Assuming a standard deviation of 0.7 mmol/l, this difference can be detected with a power (1-β) of 0.80 and an alpha of 0.05 with two groups of 64 subjects. Taking a loss to follow up of about 20% into account, a total of 160 subjects will be recruited. A significant difference of 300 grams in birth weight can also be detected with this number of participants, assuming a standard deviation of 600 grams.

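### The stated 64 per group does not follow from the stated glucose inputs: these need about 50 per group, and 64 gives power of about 0.89, not 0.80

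*Protocol article*

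**What the plan says.** The Sample size section of the protocol article gives one calculation and one supplementary statement.

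- **Basis.** "Power analysis is based on the effects of the intervention program on fasting plasma glucose".
- **Effect and spread.** "A difference of 0.4 mmol/l in fasting plasma glucose between the two research groups is considered to be clinically relevant". The next sentence begins "Assuming a standard deviation of 0.7 mmol/l".
- **Result.** "this difference can be detected with a power (1-β) of 0.80 and an alpha of 0.05 with two groups of 64 subjects". Whether alpha is one-sided or two-sided is not stated, and no adjustment for several primary outcomes is mentioned.
- **Loss.** An allowance of about 20% brings the recruitment target to 160.
- **Birth weight.** "A significant difference of 300 grams in birth weight can also be detected with this number of participants, assuming a standard deviation of 600 grams". No power is attached to this statement.

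The Outcome measurements section names fasting plasma glucose and the relative increase in insulin resistance as primary maternal outcomes, and birth weight as the primary neonatal outcome.

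**The concern.** Every input to the glucose calculation is printed, so a reader can repeat it, and the result is not 64. This is not a detail that an article leaves to a fuller protocol or to an analysis plan. It is a completed calculation whose parts disagree.

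Three things depend on it:

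- The printed justification for recruiting 160 pregnant women cannot be reproduced.
- The reader cannot tell what power the glucose comparison has. If the SD is 0.7, it is about 0.89. If the SD used in planning was 0.8, it is 0.80 with no margin.
- A reader who trusts the glucose inputs and corrects the number would conclude that 125 women are enough. That would weaken the birth-weight comparison, which needs the larger number.

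**Working it through.** **Inputs, all from the Sample size section.** Glucose difference 0.4 mmol/l, SD 0.7 mmol/l, alpha 0.05, power 0.80, equal groups, loss about 20%. Birth-weight difference 300 g, SD 600 g. Two-sided alpha is my assumption; one-sided is also tried.

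**1. The plan's glucose figure.** The standardised difference is d = 0.4/0.7 = 0.571.

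- Normal approximation: n per group = 2(1.960 + 0.842)² × (0.7/0.4)² = 2 × 7.849 × 3.0625 = 48.07, so 49.
- Noncentral t-test: 49.05, so 50.
- One-sided alpha, t-test: 38.56, so 39. Sidedness does not explain 64; it moves the answer further away.

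The stated 64 is not reproduced. It exceeds 50 by 14 per group, or 14/50 = 28%.

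**2. Glucose power at 64 per group.** The noncentrality is 0.571 × √(64/2) = 3.23.

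- Normal approximation: Φ(3.23 − 1.96) = 0.898.
- t-test: 0.894.

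The article states 0.80, so the gap is about 9 percentage points.

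**3. The loss step.** 2 × 64 = 128, and 128/(1 − 0.20) = 160. This is correct, so the discrepancy arises before the allowance for loss. The same step from 50 per group gives 100/0.80 = 125.

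**4. Birth weight.** d = 300/600 = 0.50.

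- Normal approximation: 2 × 7.849 × (600/300)² = 62.8, so 63.
- t-test: 63.77, so 64.
- Power at 64 per group, t-test: 0.801.
- Power at 50 per group, t-test: 0.697, or about 0.70.

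The birth-weight inputs therefore reproduce 64 exactly, at the power and alpha that the paragraph attaches to glucose.

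**5. Other changes that also land at or near 64.** Each row changes one element of the glucose calculation and keeps the rest as printed.

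| Change | n per group |
|---|---|
| SD 0.8 instead of 0.7 | 63 (normal), 64 (t) |
| Difference 0.35 instead of 0.4 | 63 (normal), 64 (t) |
| Power 0.90 instead of 0.80 | 65 (normal), 66 (t) |
| Alpha 0.05/3, split over three primary outcomes | 65 (normal), 66 (t) |
| 50 already raised for 20% loss (50/0.80 = 62.5), then raised again | 63 |

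The first two give 64 because 0.4/0.8 and 0.35/0.7 both equal 0.50, the same standardised difference as birth weight. Arithmetic alone cannot separate these explanations.

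**The case against.** **The error is on the safe side.** On the printed inputs, 64 per group gives the glucose comparison more power than claimed. No test, estimate or recruitment target changes. This stands, and it limits how serious the point is. It would cease to hold only if the glucose SD or difference were itself misprinted, which the article does not show.

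**160 is not too many.** Birth weight is also a primary outcome and needs 64 per group at 80% power. The figure of 125 applies to glucose alone. This stands too, and is the reason to leave the target as it is.

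**A reader might infer that birth weight really set the size.** The match is exact, so the inference is tempting. The article does not support it as fact: it names glucose as the basis, presents birth weight as an additional difference that the same number can detect, and gives no power for it. The other changes in the table fit about as well.

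**A reader might also infer that the stated power or the stated SD must be wrong.** That is too narrow, since the difference, an unstated split of alpha or a double allowance for loss could equally be the source. The two inferences also do not sit together. If the SD meant was 0.8, glucose itself requires 64 and the stated basis is true. If birth weight fixed the number, the SD of 0.7 may well be right, and only the power quoted for glucose is wrong.

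**Knock-on effects on an alpha allocation or a blinded check of the SD** cannot be claimed, because the article describes neither procedure.

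**Conclusion.** The paragraph is wrong as written. With a difference of 0.4 mmol/l, SD 0.7 mmol/l, alpha 0.05 and power 0.80, about 50 per group are needed, not 64; with 64 per group, power is about 0.89, not 0.80. This assumes a two-sided comparison of two means with equal groups. A one-sided test widens the gap, and the choice between the normal approximation and the t-test moves the answer by one woman per group.

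The document does not establish which element is at fault. The number agrees with the birth-weight inputs at 80% power, and it would agree as well with a changed glucose SD or difference. What can be said is that the stated inputs, power and number cannot all be right together for glucose.

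This is an error in the reported justification. It is worth correcting but does not endanger the trial: on the printed inputs it is conservative, and both outcomes with a stated effect and SD have power of at least 0.80 at 64 evaluable women per group.

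**What to change.** The sponsor should check the planning records, confirm which outcome or input fixed 64 per group, and restate the Sample size paragraph accordingly.

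- **If the glucose inputs stand:** say that 64 evaluable women per group give power of about 0.89 for 0.4 mmol/l with SD 0.7 mmol/l, and about 0.80 for 300 g with SD 600 g, both at two-sided alpha 0.05. Name birth weight as the outcome that fixed the number only if the records show it.
- **If a glucose input was misprinted** (for example SD 0.8 or a difference of 0.35 was used): correct that input. The stated power of 0.80 and 64 per group then agree.
- **If another power, a split alpha or an earlier allowance for loss was used:** state it, and rework the figures to match.

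In every case, give the sidedness of alpha and the power for each of the two outcomes. Keep the target of 160: reducing to 50 evaluable women per group would cut birth-weight power to about 0.70.

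The cost is a look at the planning records and the rewording of one paragraph, with no change to recruitment.
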